## Abstract

Infection with the SARS-CoV-2 virus seems to contribute significantly to increased postoperative complications and mortality after emergency surgical procedures. Additionally, the fear of COVID-19 contagion delays the consultation of patients, resulting in the deterioration of their acute diseases by the time of consultation. In the specific case of urgent digestive surgery patients, both factors significantly worsen the postoperative course and prognosis. Main working hypothesis: infection by COVID-19 increases postoperative 30-day-mortality for any cause in patients submitted to emergency/urgent general or gastrointestinal surgery. Likewise, hospital collapse during the first wave of the COVID-19 pandemic increased 30-day-mortality for any cause. Hence, the main objective of this study is to estimate the cumulative incidence of mortality at 30-days-after-surgery. Secondary objectives are: to estimate the cumulative incidence of postoperative complications and to develop a specific postoperative risk propensity model for COVID-19-infected patients.

A multicenter, observational retrospective cohort study (COVID-CIR-study) will be carried out in consecutive patients operated on for urgent digestive pathology. Two cohorts will be defined: the “pandemic” cohort, which will include all patients (classified as COVID-19-positive or -negative) operated on for emergency digestive pathology during the months of March to June 2020; and the “control” cohort, which will include all patients operated on for emergency digestive pathology during the months of March to June 2019. Information will be gathered on demographic characteristics, clinical and analytical parameters, scores on the usual prognostic scales for quality management in a General Surgery service (POSSUM, P-POSSUM and LUCENTUM scores), prognostic factors applicable to all patients, specific prognostic factors for patients infected with SARS-CoV-2, postoperative morbidity and mortality (at 30 and 90 postoperative days). The main objective is to estimate the cumulative incidence of mortality at 30 days after surgery. As secondary objectives, to estimate the cumulative incidence of postoperative complications and to develop a specific postoperative risk propensity model for SARS-CoV-2 infected patients.

The protocol (version1.0, April 20th 2020) was approved by the local Institutional Review Board (Ethic-and-Clinical-Investigation-Committee, code PR169/20, date 05/05/20). The study findings will be submitted to peer-reviewed journals and presented at relevant national and international scientific meetings.

ClinicalTrials.gov Identifier: NCT04479150 (July 21, 2020).

Strengths and limitations of this studyThe multicentric design of the study will allow the recording of a large number of operated patients.The specific emergency digestive pathology considered and the recording of clinical conditions and prognostic scores will reduce the heterogeneity of population included in this study.The impact of SARS-CoV-2 viral status, COVID-19-related prognostic factors, the validity of surgical prognostic scores and the specific characteristics of initial pandemic period in Spain (March–June 2020) on postoperative outcomes will be assessed.The control cohort (same period, 2019) will represent a proper comparative group.Due to the retrospective design of the study, and the very first contact of Spanish Health System with the COVID-19 at the beginning of the study period, some data may be lost.

## Introduction

1

Since early 2020, the rapid spread of the pandemic due to the SARS-CoV-2 virus (coronavirus 2 of severe acute respiratory syndrome) has triggered a complex and profound global sanitary, social, and economic crisis.^[1–4]^ As of August 7th, 2020, the pandemic has infected more than 18.9 million people, with a devastating death toll of more than 709,500 worldwide (official data from the World Health Organization, WHO).^[2,5]^ Spain, with more than 314,300 confirmed cases and more than 28,500 deaths, constitutes one of most severely hit countries (official data as of 08/07/20 from the Ministry of Health, Consumption and Social Welfare, Spain).^[6,7]^ Multiple clinical guidelines, protocols and recommendations have been developed to standardize medical practice and protect both patients and professionals.^[8–11]^ All health specialties have adopted forceful contingency plans and a profound reorganization of their healthcare activity.^[7,11]^ Emergency digestive surgery has not been different.^[11–15]^ During the period of maximum impact of the pandemic, most scheduled surgical interventions were drastically reduced or suspended, operating rooms were converted into critical care units, and highly versatile surgical staff were redistributed to medical services.^[14,16–20]^ However, urgent and “non-delayable” interventions continued to be performed in patients who were occasionally infected with SARS-CoV-2.^[13,20–23]^

Some publications suggest that surgical procedures accelerate and exacerbate the clinical progression of COVID-19.^[17,24]^ Several teams have recently described classic emergency surgical pathologies with “atypical” forms of presentation and/or complicated postoperative evolution, differing from the usual “pre-pandemic” scenario.^[10,13,25–28]^

Urgent and emergency digestive interventions, extremely prevalent in our setting, are always associated with a high risk of complications and mortality, compared to elective surgeries.^[29,30]^ In the current context of the COVID-19 pandemic, in addition to the preoperative risk factors and the peculiarities inherent in all emergency surgery, other different elements seem to influence the worst postoperative prognosis, even in COVID-19-negative patients.^[21,31]^ Several factors may be involved:

1.patients’ fear of visiting the hospital during the pandemic (and/or home confinement) makes that clinicians face with more advanced surgical pathologies in the moment of consultation;2.“saturation” of the health system, collapse of the emergency departments, and the misinterpretation of septic symptoms in this context can easily add an “extra” delay in diagnosis;3.conservative treatment (nonsurgical management) may be forced beyond usual local standards, making patients who ultimately need a surgical rescue worse off;4.work overload of supporting services, such as intensive care units and interventional radiology, may increase “failure to rescue” in complicated patients, not just COVID-19-positive patients.^[16,21–23,32–35]^

Furthermore, we can’t exclude a synergistic negative effect of SARS-CoV-2 infection on the acute disease that prompted surgical consultation.^[35]^

The COVID-19 pandemic seems to directly or indirectly modify the clinical profile of the urgent surgical pathology treated in a General Surgery Emergency Department (epidemiology, surgical indications, clinical severity, diagnostic delay, complications, etc.).^[21,36]^ The surgical indications and operative techniques for urgent digestive surgeries performed during the “pandemic” period may differ from the “pre-pandemic” period, as well as the postoperative complication and mortality rates of COVID-19-negative patients during the pandemic period.^[21,23,25,37]^

Digestive surgeons ask several questions in this particular epidemiological context:

1.To what extent does COVID-19 infection modify the nature, clinical profile, or postoperative evolution of urgent surgical pathology?;^[17,21,26]^2.Does the socio-sanitary context of a pandemic modify the presentation, severity, diagnostic delay, or postoperative evolution of COVID-19-negative patients undergoing emergency surgery?;^[21,32]^3.Do the usual postoperative risk prediction scales maintain their validity in this period or do they require any kind of adjustment based on other specific prognostic criteria?;^[38,39]^4.Is it appropriate to perform emergency surgical interventions with the classic clinical indications or should some acute pathologies be deferred and the surgery be postponed until normal conditions prevail?;^[10,15,25,36,37]^5.Are all the surgical techniques and approaches commonly used in emergency digestive surgery equally safe during COVID-19 pandemic period?^[9,23,33,36,37,40]^

These and other questions should be answered as soon as possible. The analysis of real data on urgent gastrointestinal surgery in patients operated on during this period could provide the necessary information.^[36,41]^ However, in order to control the confounding factors of the pandemic scenario, cohort studies should provide additional information on the pathology and clinical condition of patients at the time of urgent surgery, for example with prognostic surgical scores. The classic surgical prognostic scales validated for the estimation of postoperative risk (scores POSSUM-mortality, POSSUM-morbidity, P-POSSUM, LUCENTUM-logistic regression, and LUCENTUM-CHAID) may not be adequate in patients undergoing emergency surgery during the pandemic period.^[38,39,42–45]^ Therefore, it may be necessary to consider other prognostic factors and design a new and specific prediction model for patients infected with SARS-CoV-2.^[46,47]^ Currently, we only have extrapolated prognostic scores for the set of COVID-19-positive patients, with little data on the specific subgroup of surgical patients, and even less information on the postoperative evolution after urgent digestive surgery.^[15,21,22,48–51]^

It would also be advisable to compare a COVID-19-positive group of patients with a simultaneous COVID-19-negative group (both in the “pandemic period”) and with a “pre-pandemic” control group in the same hospitals.

A registry of these characteristics would provide firmer evidence on their clinical profile and would make it possible to adequately estimate patient's postoperative risk.^[46]^ The few studies published to date address these issues superficially, with unadjusted raw data and a low degree of statistical analysis and scientific evidence.^[10,35,52]^

To contribute to the clarification of these doubts, we propose a multicenter, observational study (“COVID-CIR” study), in which multiple digestive surgical teams from different areas of Spain severely affected by the COVID-19 pandemic will participate. Main working hypothesis: infection by COVID-19 increases postoperative 30-day mortality for any cause in patients submitted to emergency/urgent general or gastrointestinal surgery. Likewise, hospital collapse during the first wave of the COVID-19 pandemic increased 30-day mortality for any cause in COVID-19-non-infected patients who required emergency/urgent general or gastrointestinal surgery. Hence, the main objective of this study is to estimate the cumulative incidence of mortality at 30 days after surgery. Secondary objectives are: to estimate the cumulative incidence of postoperative complications and to develop a specific postoperative risk propensity model for COVID-19 infected patients.

The conclusions of this study could contribute to design a future action plan for similar epidemiological situations or subsequent outbreaks of SARS-CoV-2.^[20,41,53]^

## Methods and analysis

2

This protocol is reported in accordance with the STROBE guideline.^[54]^

### Study design

2.1

COVID-CIR is an observational, multicenter, cohort study of patients undergoing emergency/urgent gastrointestinal surgery during the period of maximum impact of the COVID-19 pandemic in Spain (from March 1st to June 30th, 2020).^[6,13]^

This study was registered in the ClinicalTrials.gov Protocol Registration and Results System (Identifier: NCT04479150, July 21st, 2020).

#### Ethical issues

2.1.1

The study conforms to the stipulations of the Declaration of Helsinki. The protocol was approved by the local Institutional Review Board (Ethics and Clinical Investigation Committee of the Hospital Universitari de Bellvitge, code PR169/20, date approval 05/05/20) and a waiver for written informed consent was given, as no additional procedures or information will be required from participants beyond that which would normally take place as part of clinical care. The list of local Institutional Review Board members is available at https://bellvitgehospital.cat/es/investiga-con-nosotros/ceic/composicion (accessed on August 11th, 2020). The level of protection of confidentiality, in terms of protection of personal data as required by Spanish Law (Organic Law on Data Protection 3/2018), is also ensured. The study findings will be submitted to peer-reviewed journals and presented at relevant national and international scientific meetings.

### Settings

2.2

A total of 30 surgical teams from different Spanish hospitals have been proposed to participate in this study (see Supplementary data file 1), which has been coordinated by the Department of General and Digestive Surgery of the Bellvitge University Hospital (L’Hospitalet de Llobregat, Barcelona, Spain). All hospitals participating are from Spain, with different surgical capabilities.^[55]^

### Study population

2.3

Patients operated on for emergency/urgent gastrointestinal surgery constitute the target population. Table 1 shows the list of all the urgent gastrointestinal surgery procedures under study. There is no patient or public involvement in the design, conduct, reporting, or dissemination plans of the study.

Inclusion criteria: ≥18 years, both genders, and operated on for urgent/emergency gastrointestinal pathology.Exclusion criteria: patients who have undergone a scheduled surgical intervention or patients operated on by a service other than General and Digestive Surgery.

**Table 1 T1:** Urgent gastrointestinal surgical procedures according to the degree of surgical complexity.

• Minor Complexity
- Hernia/eventration
- Perianal surgery, pilonidal sinus
• Moderate Complexity
- Cholecystectomy (open or laparoscopic)
- Appendectomy (open or laparoscopic)
• Major Complexity
- Gastrointestinal perforation suture
- Intestinal resection
- Colectomy
- Main bile duct surgery
- Gastrectomy
- Lysis of adhesions or reduction of internal hernia or enterolithotomy
- Splenectomy or minor liver trauma
- Exploratory laparotomy
- Surgical hemostasis due to hemoperitoneum
• Major + Complexity
- Open pancreatic necrosectomy
- Pancreatectomy
- Damage control surgery (due to trauma, bleeding, ischemia or peritonitis)
• Others

Two cohorts will be defined:

1.Cohort A: consecutive patients who required emergency/urgent gastrointestinal surgery from March 1st to June 30th, 2020 (“first wave” of the COVID-19 pandemic in Spain). This cohort will be stratified by SARS-CoV-2 infection status (according to the RT-PCR [Reverse Transcription-Polymerase Chain Reaction] test, or serological detection of antibodies):^[8,11,14,17,46]^COVID-19-positive patients (infected by SARS-CoV-2), andCOVID-19-negative patients (not infected by SARS-CoV-2).2.Cohort B: consecutive patients who required emergency/urgent gastrointestinal surgery from March 1st to June 30th, 2019 (control cohort of a “pre-pandemic” period).

Figure 1 shows the flow diagram of the study. Table 2 shows the complete list of postoperative complications and Table 3 shows the Clavien-Dindo classification for complications.^[56,57]^

**Figure 1 F1:**
[figure not shown]
Flow diagram of the study.

**Table 2 T2:** Listing and description of postoperative complications.

• Anastomotic dehiscence/intestinal fistula: clinical or radiological data of extravasation of intestinal content through an anastomosis, drainage, surgical wound, or abnormal hole
• Superficial wound dehiscence (full fascia)
• Evisceration (clinical or radiological; includes any degree)
• Heart failure or acute pulmonary edema: symptoms or signs of left or congestive ventricular insufficiency (change from preoperative situation)
• Fever of unknown origin: mantained fever >37°C for ≥24 hours, of unknown cause, after usual immediate postoperative temperature increase
• Mild hemorrhage: postoperative hemorrhage that does not require surgical re-examination or endoscopic/radiological procedure for treatment
• Severe bleeding: postoperative hemorrhage that does require surgical re-examination or endoscopic/radiological procedure for treatment
• Hypotension: maintained drop of systolic pressure to <90 mm Hg for >24 hours, detected with sphygmomanometer or arterial catheter
• Superficial wound infection: redness and pain around the surgical wound or local suppuration
• Deep wound infection: intra-abdominal collection (abscess), clinically or radiologically confirmed, or release of purulent content through a drainage
• Respiratory infection or pneumonia: purulent sputum with positive bacteriological/virological culture, with or without changes in chest X-ray, or fever with pulmonary radiological consolidation
• Urinary tract infection: urinary symptoms or fever, associated with sediment with bacteriuria/leukocyturia or positive urine culture
• Renal failure: sharp increase in creatinine to ≥2 mg/dl (≥177 μmol/L) in patients with normal prior renal function, or a sharp increase in creatinine (>50%) in patients with chronic kidney failure, or need for renal replacement therapy
• Respiratory failure: breathing difficulty requiring emergency ventilatory support, or PaO_2_ <60 mm Hg and PaCO_2_ >45 mm Hg breathing ambient air
• Bacteremia-Sepsis: positive blood culture
• DVT (deep vein thrombosis) and/or PE (pulmonary embolism): clinical suspicion, radiological confirmation by ECO-doppler, chest-computed tomography or ventilation/perfusion scan, or *postmortem* diagnosis
• Postoperative ileus
• Pleural effusion/pulmonary atelectasis
• Intestinal perforation
• Seroma or surgical wound hematoma
• Intestinal occlusion
• Ostomy complications (bleeding, retraction, infection, dermatitis, fistula, stoma necrosis)
• Blood glucose disturbances maintained >24 hours
• Atrial fibrillation
• Hypertensive crises (systolic blood pressure >200 mm Hg and/or diastolic blood pressure >120 mmHg)
• Acute confusion syndrome
• Gastrointestinal bleeding (upper or lower)
• Acute myocardial infarction, cerebrovascular accident or acute limb ischemia (peripheral artery ischemia)
• Acute mesenteric ischemia (intestinal ischemia, small bowel or colon)
• Cardiomyopathy or pericarditis

**Table 3 T3:** Severity of postoperative complications according to Clavien-Dindo system.

Degree	Definition
I	Any deviation from the normal postoperative course that does not require surgical, radiological or endoscopic intervention. Includes additional use of electrolyte solutions, diuretics, antiemetics, antipyretics, analgesics and physiotherapy. Includes superficial infection or seroma/hematoma treated at the bedside.
II	Different pharmacological treatment than the above ones is required, including blood transfusions, antibiotics and total parenteral nutrition.
III	Requires surgical, endoscopic or radiological intervention:
a	No general anesthesia
b	Under general anesthesia
IV	Life-threatening complication requiring treatment in intermediate or intensive care unit:
a	Single organ dysfunction (includes haemodialysis)
b	Multiple organic dysfunction
V	Patient death

### Study timeline

2.4

The study period has been delimited by the period of the “COVID-19 pandemic”: March 1st to June 30th, 2020. In Spain, this period corresponds to the maximum impact of the pandemic on health services (due to contingency plans and the reorganization of medical services) and society at large (due the “state of alarm” implemented by the Spanish government, which resulted in home confinement, restrictions on mobility and other preventive measures).^[6]^

Schedule the study protocol was drawn up in March and April 2020. The IRB (Institutional Review Board) approved the protocol on May 5, 2020 (code PR169/20, date 05/05/20).

At the moment of submitting this manuscript, participant recruitment is in progress. The inclusion of patients data does not end until August 31st, 2020. Provided the 30-day follow-up of the last included patient is completed by July– to August 2020, and that 1 month will be required for database cleaning and statistical analysis, it is expected that the first results (including ≤30-day morbidity/mortality) will be available in September to October 2020. Complete analysis (including ≤90-day mortality) will be available in November to December 2020. Table 4 depicts the study schedule.

**Table 4 T4:** Study schedule.

		Follow-up		
Data	Enrollment^∗^	Day of hospital discharge/death	Day 30 of surgery	Day 90 of surgery
Inclusion/exclusion criteria	✓			
Day of surgery	✓			
Demographic data^†^	✓			
Clinical data^†^	✓			
Prognostic scores (see Table 5)	✓			
Presurgery evaluation	✓			
Urgent surgery characteristics (see Table 1)	✓			
Postsurgery evaluation: Mortality		✓	✓	✓
Postsurgery evaluation: Morbidity (see Table 2)		✓	✓	
In cohort 2020, COVID-19-positive:				
• RT-PCR or serological detection	✓			
In cohort 2020, COVID-19-positive:				
• COVID-19-related complications^‡^		✓	✓	

### Outcomes

2.5

The primary outcome is the cumulative incidence of mortality for any cause at 30 days after urgent gastrointestinal surgery.Secondary outcomes are:

1.Cumulative incidence of all-causes mortality within 90 days after surgery.2.Cumulative incidence of any postoperative morbidity within 30 days after surgery: overall postoperative complications and/or complications specifically associated with the evolution of COVID-19 (Table 2).^[8,58]^3.Cumulative incidence of severe 30 day-postoperative complications, >IIIA grade according to the Clavien-Dindo score (Table 3).^[56,57,59]^4.Failure-to-rescue defined as the percentage of patients dying of any cause as a consequence of any postoperative complication.5.Length of hospital stay (from the day of admission to the date of hospital discharge or death).6.“Physiological” and “operative severity” to calculate the estimated risks of mortality and postoperative complications according to 5 surgical prognostic scales (Table 5): POSSUM-mortality and POSSUM-morbidity scores, P-POSSUM score, LUCENTUM-logistic regression, and LUCENTUM-CHAID scores.^[14,38,39,42–45]^7.Attitude of the surgeons due to the influence of the SARS-CoV-2 pandemic regarding the “moment of surgical intervention”:^[21,22,32,33]^ Did it change? [No/Yes]; if affirmative:-Was the patient probably seen for consultation later than usual (more advanced pathology)?-Was the diagnosis of the surgical pathology delayed?-Was urgent intervention delayed for logistical problems (“hospital” delay)?-Was a conservative/non-operative treatment “over-indicated”?8.Attitude of the surgeons due to the influence of the SARS-CoV-2 pandemic regarding the “surgical technique” used:^[9,10,15,36,37,40]^ Did it change? [No/Yes]; if affirmative:-Was the surgical technique being “more conservative than usual” or “more aggressive than usual”?

**Table 5 T5:** Postoperative prognostic scores.

Score	Equation	Prediction
POSSUM (mortality)	Ln [R/(1–R)] = –7.04 + (0.13 × physiological score) + (0.16 × operative severity score)	Postoperative mortality
POSSUM (morbidity)	Ln [R/(1–R)] = –5.91 + (0.16 × physiological score) + (0.19 × operative severity score)	Postoperative morbidity
P-POSSUM	Ln [R/(1–R)] = –9.065 + (0.1692 × physiological score) + (0.155 × operative severity score)	Postoperative mortality
LUCENTUM-logistic regression	Ln [R/(1–R)] = –4.461 + (0.257 × age) + (0.261 × sodium) + (0.167 × Hb) + (0.364 × white cell count) + (0.397 × operative severity)	Postoperative morbidity
LUCENTUM-CHAID	Ln [R/(1–R)] = –5.835 + (0.757 × cardiac function) + (0.563 × sodium) + (0.411 × peritoneal soiling) + (0.778 × operative severity)	Postoperative morbidity

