### Data collection

2.6

All data will be gathered from electronic medical record. All consecutive patients operated on for urgent digestive surgery during the study period will be screened and included if they fulfil the inclusion criteria.

Demographic characteristics, comorbidities, clinical and analytical variables, SARS-CoV-2 infectious status (pre- and post-operative periods), clinical diagnosis, intraoperative findings and postoperative course (30-day morbidity, 30-day reinterventions, hospital stay, 30-day readmissions, and mortality at 30 and 90 days) will be recorded (Supplementary data file 2).^[25,35]^

All values necessary for the automatic calculation of the surgical prognostic scores shall also be included (Table 5).^[39,45]^

Prognostic factors recently described in COVID-19-positive patients will also be recorded: advanced age, hypertension, smoking, diabetes, chronic obstructive pulmonary disease (COPD), cardiovascular history, lymphocyte and platelet count, alanine-aminotransferase (ALT), C-reactive protein (CRP), D-dimer, ferritin, procalcitonin (PCT), lactate-dehydrogenase (LDH), troponin, prothrombin time, “neutrophil-to-lymphocyte ratio” (NLR) and “platelet-to-lymphocyte ratio” (PLR).^[8,11,16,26,35,49,50,60–64]^

Among postoperative complications, those currently considered “characteristics” of COVID-19 (pneumonia, respiratory failure, venous thromboembolism, acute myocardial infarction, cerebrovascular accident, peripheral arterial ischemia, intestinal ischemia, cardiomyopathy, or pericarditis) will be analyzed in depth.^[8,35,58]^

An electronic Case Report Form (eCRF), based on REDCap platform *(Research Electronic Data Capture software, REDCap Consortium)*, has been created *ad hoc* for this study (Supplementary data file 3).^[65]^

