### Sample size

2.8

Due to the exploratory nature of our aim, no formal calculation of sample size was performed. It will be defined by the total number of patients who underwent emergency gastrointestinal surgery during the 2 study periods at the participating hospitals. We expect to include more than 2000 patients.

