### Statistical analysis

2.9

Baseline characteristics will be described using standard descriptive statistics, and a descriptive and exploratory comparative analysis between both cohorts will be carried out.

The cumulative incidence of mortality (and its 95% confident interval) and the incidence of morbidity (and its 95% confident interval) at 30 and 90 days will be estimated by positive/negative SARS-CoV-2 infection status (cohort A) and in the control group (cohort B).

To minimize the selection bias effect of potential confounders, propensity scores will be estimated using a multinomial model to estimate the probability that subjects were SARS-CoV-2-positive, SARS-CoV-2-negative or control. Subjects will be matched using the propensity scores. After matching, to identify imbalance between groups, the standardized mean difference will be estimated and plotted. In the matched sample, the cumulative incidence of mortality (and its 95% confidence interval) and the incidence of morbidity (and its 95% confidence interval) at 30 and 90 days will be compared using a generalized linear model with a binomial distribution and a logarithm link function. Those variables that remain imbalanced between groups after matching would be added to the model with an adjusting purpose.

A generalized linear model with a binomial distribution and a logarithm link function will be used to estimate relative risk as a measure to indentify prognostic factors associated with 30 and 90 days mortality and morbidity incidences. Five predictive scores of postoperative morbidity and/or mortality will be calculated according with Table 5: POSSUM-mortality, POSSUM-morbidity, P-POSSUM, LUCENTUM-logistic regression, and LUCENTUM-CHAID.^[38,39,42–45]^ Their applicability on postoperative morbidity or mortality prediction in COVID-19 pandemic will be assessed.

Data analysis will be carried out using R version 4.02 or superior (R Core Team, 2019; R: A language and environment for statistical computing. R Foundation for Statistical Computing, Vienna, Austria. URL https://www.R-project.org/).

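### Hospital stay ends at discharge or death alike, so comparing it between groups expected to differ in mortality mixes recovery time with time to death

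*Protocol article*

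**What the plan says.** Section 2.5 (Outcomes) of the protocol article lists as its fifth secondary outcome "Length of hospital stay (from the day of admission to the date of hospital discharge or death"). Both events end the interval, with no distinction between them. Nothing elsewhere in the article restricts this outcome to survivors, treats death as a competing event or gives death an unfavourable value.

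The Introduction states two hypotheses about mortality. One is that "infection by COVID-19 increases postoperative 30-day mortality for any cause in patients submitted to emergency/urgent general or gastrointestinal surgery". The other is that "hospital collapse during the first wave of the COVID-19 pandemic increased 30-day mortality for any cause in COVID-19-non-infected patients". So all three groups (infected 2020, non-infected 2020 and 2019 control) are expected to differ in mortality.

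Section 2.9 (Statistical analysis) says that mortality and morbidity "will be compared using a generalized linear model with a binomial distribution and a logarithm link function". It names no method for length of stay. Section 2.6 (Data collection) records "30-day reinterventions, hospital stay, 30-day readmissions, and mortality at 30 and 90 days", and Table 4 has an assessment on the day of hospital discharge or death at which mortality is noted.

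**The concern.** Length of stay is usually read as a measure of recovery, with shorter meaning better. Under this definition a patient who dies on day 3 and a patient who goes home well on day 3 score the same. The recorded stay of a patient who dies in hospital is cut off, and the share of patients cut off grows with mortality.

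That would matter little if mortality were alike across groups, but the study is built on the expectation that it is not. A difference in mean or median stay could then reflect different recovery among those who leave alive, different numbers of deaths, different timing of deaths, or a mixture. A real lengthening of recovery in infected survivors could be hidden or exaggerated, and the number alone would not show which.

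**Working it through.** **No figure to reproduce.** The article gives no expected stay, mortality rate or time to death, and states that "no formal calculation of sample size was performed". Every number below is therefore an assumption chosen to show the mechanism.

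**1. Mean stay of a group.** Let m be in-hospital mortality, S the mean stay of patients discharged alive and D the mean time from admission to death.

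Mean stay = (1 − m) × S + m × D.

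If S and D are the same in both groups, the higher-mortality group minus the lower-mortality group is (m_high − m_low) × (D − S). The sign depends only on whether deaths come before or after typical discharge. The mortality gap sets the size.

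**2. Numbers.** Take S = 12 days in both groups, and mortality of 3% and 25%.

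| Mean time to death D | Mean stay at 3% | Mean stay at 25% | Difference |
|---|---|---|---|
| 6 days | 0.97×12 + 0.03×6 = 11.82 | 0.75×12 + 0.25×6 = 10.50 | −1.32 |
| 12 days | 12.00 | 12.00 | 0 |
| 18 days | 0.97×12 + 0.03×18 = 12.18 | 0.75×12 + 0.25×18 = 13.50 | +1.32 |

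The closed form agrees: 0.22 × (±6) = ±1.32. Patients discharged alive do not differ in any row.

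**3. Other inputs, same pattern.** With mortality of 4% versus 20% and S = 10, the difference is −1.28 days at D = 2, −0.80 at D = 5, 0 at D = 10 and +1.60 at D = 20. With S = 6 it is −0.64 at D = 2, −0.16 at D = 5 and +0.64 at D = 10. The shorter the survivors' stay, the earlier the sign turns.

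**4. Simulation of the cut-off** (400,000 patients per scenario). The stay each patient would have had without dying is log-normal with median 6 days and sigma 0.8. Time to death is log-normal with sigma 0.8. The recorded stay of a patient who dies is the earlier of the two.

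- Same would-be stay for everyone, median time to death 3 days, mortality 4% versus 20%: mean recorded stay is 8.03 versus 7.24 days and the median 5.80 versus 5.04, so the higher-mortality group looks better. Patients discharged alive have practically equal means (8.24 versus 8.26). If deaths are ranked as the worst result, the medians are 6.25 versus 7.75 and the order reverses.
- Patients who die would have stayed three times as long, median time to death 15 days: mean recorded stay is 8.45 versus 9.16 days, so the higher-mortality group now looks worse. Patients discharged alive are again practically equal (8.27 versus 8.24).

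**5. What the alternative does.** The cumulative incidence of live discharge cannot exceed 1 minus in-hospital mortality. In the example of step 2, if every survivor has left by day 30, it reaches 97% and 75% by day 30 in all three rows. Moving the deaths earlier or later within the stay does not change which group comes out worse.

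**The case against.** Four arguments can be made for leaving the outcome as it is.

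- **No comparison is specified.** Section 2.9 names models only for mortality and morbidity, and a journal article may leave the handling of stay to a fuller document. The absence of a named model is indeed no fault. But the end of the interval is not left open: section 2.5 fixes it, and any group comparison that follows the definition as written inherits the mixture.
- **For bed use the definition is right.** A bed is freed by death as much as by discharge, and the Discussion names resource management among the intended uses. The outcome also carries no statement that shorter is better. This stands for a description of occupancy. It does not make a pooled group difference readable as a difference in recovery.
- **The direction is not known.** This stands. A reader might infer that the definition always flatters the group with more deaths. The documents do not support that: they give no times to death. Table 1 includes hernia, perianal surgery, appendectomy and cholecystectomy, for which short stays are plausible, so deaths may well fall after typical discharge.
- **The consequence is limited.** This is one of eight secondary outcomes in a study that calls its aim exploratory, and mortality is estimated for the same three groups. This stands too, and it bounds the importance of the point.

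A reader might also infer that the stay stops at the first discharge, so that a patient sent home early and readmitted scores too well. Section 2.5 does not say first discharge, and section 2.6 lists 30-day readmissions as a separate item, so that criticism is not made here.

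**Conclusion.** The concern holds in a conditional form. As defined, length of stay cannot be interpreted as recovery when compared between groups with different mortality, and this study expects exactly such a difference. The distortion can go either way: the higher-mortality group looks better if deaths precede typical discharge and worse if they follow it. With an assumed 12-day survivor stay and 3% versus 25% mortality, it runs from 1.3 days shorter to 1.3 days longer as mean time to death moves from day 6 to day 18. These sizes are illustrative, because neither the mortality rates nor the stays nor the times to death come from the documents. That the measure mixes two processes follows from the definition itself and needs none of these figures. The primary outcome is untouched. The change is worth making because it is cheap and the outcome is otherwise easy to misread.

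**What to change.** For the comparison between groups, redefine secondary outcome 5 as time to discharge alive, with in-hospital death as a competing event, reported as the cumulative incidence of live discharge by day 30. State whether day 30 counts from admission, as the stay now does, or from surgery, as the follow-up in Table 4 does. Show the cumulative incidence of in-hospital death next to it, since fewer live discharges can reflect either more deaths or slower recovery.

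If raw length of stay is kept, for example for bed use, report it descriptively and separately for patients discharged alive and patients who died, beside mortality. The figure for those discharged alive should stay descriptive, because it conditions on survival.

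The cost is a change of wording and a modest extra analysis. Hospital stay, mortality and status at discharge or death are already recorded. The drawback is a slightly less direct comparison with papers that report raw stay. Days alive and out of hospital would be an option only if the duration of readmissions is collected, which the article does not show.
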